This concept was recently proven in a pair of randomized trials investigating the efficacy of a case-management collaborative care model for patients with diabetes and depression in the primary care setting of Group Health Cooperative in Washington State [28,29]. In the first trial, a case-management approach proved effective in reducing depressive symptoms, but did not result in improved glycemic control [28]. In the second study, the case-managed collaborative care model was expanded in scope, aimed at achieving improvements of depressive symptoms and cardio-metabolic markers in individuals with depression and poorly controlled diabetes or heart disease [29]. In both cases, a nurse care manager guided patient-centered care with family physicians and consultant physician specialists. In the second study the intervention initially focused on the treatment of depression, but also aimed at management of diabetes and cardiovascular risk factors (e.g. high blood pressure, elevated lipids, elevated A1c), as well as lifestyle health-related behaviors. The trial involved 214 patients from 151 physicians in 14 primary care clinics. Patients in the intervention group had greater overall 12-month improvement across A1c (difference, 0.58%), LDL cholesterol (difference, 0.2 mmol/L), systolic blood pressure (difference, 5.1 mm Hg), and SCL-20 depression scores (difference, 0.40 points) (P < 0.001). Patients in the intervention group also were more likely to have one or more adjustments of antihypertensive medications (P < 0.001), insulin (P = 0.006), and antidepressant medications (P < 0.001), and they had better quality of life (P < 0.001) and greater satisfaction with care (P < 0.001). Patients in the intervention group had a mean of 10.0 in-person and 10.8 telephone visits with the nurse care manager over the 12-month period. The estimated mean cost per patient for this intervention, including all nurse contacts, specialist physician consultations, and information system support, was $1,224 (USD) in 2009 [29]. However, these intervention costs were offset by savings in total medical costs; over a 24-month period the intervention was associated with approximately $600 cost savings per patient compared to usual primary care [30].

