### Hypotheses

We hypothesize the TeamCare-PCN intervention will reduce depressive symptoms, increase achievements of targets for cardio-metabolic measures, improve lifestyle behaviors, and be cost-effective. Furthermore, we anticipate this intervention will be acceptable and feasibly implemented in the PCN environment.

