### Eligibility criteria

Inclusion Criteria:

 · Have type 2 diabetes and under the care of a PCN family physician and be

 · 18 years of age or older and

 · Score > =10 on the PHQ-9 [29,39,40] and

 · Speak English and have adequate hearing to complete telephone interviews and

 · Be willing and able to provide written informed consent to participate

Exclusion Criteria:

 · Severe and/or terminal physical illness (e.g. heart disease, renal failure, cancer, major organ failure) or

 · Serious and/or severe mental or psychiatric illness (e.g. bi-polar disorder or schizophrenia, use of anti-psychotic or mood stabilizer medication, or cared for by a psychiatrist); patients taking anti-depressants or receiving supportive psychotherapy from non-psychiatrists would be eligible or

 · Pregnant or breastfeeding or

 · Live in long-term care facility or

 · Already participating in other clinical trials

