Stepped care/treat-to-target algorithms for Phase 2 (cardio-metabolic care) were developed in collaboration with health care professionals at the PCNs and study specialists using local and national guidelines. Phase 2 includes working with the CM in analogous fashion to Phase 1, but with a focus on reaching individualized targets for hemoglobin A1c, lipids and blood pressure measures. Phase 3 involves patient education to address lifestyle behaviors such as diet and exercise. Locally developed educational materials and existing PCN support programs will be available for patient referrals.

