#### Chronic disease-related clinical outcomes

Clinical outcome measures include systolic blood pressure (SBP), LDL cholesterol and A1c, demonstrated by achievement of targets or significant improvements as indicated with a 10% improvement over baseline [59,60]. These outcomes will be measured using point-of-care devices that we have standardized and placed in each PCN. Capillary blood samples will be collected from participants to assess A1c and lipid profile. Cardiovascular (blood pressure and resting heart rate) and anthropometric (weight, height, and waist circumference) measurements will also be assessed at clinic visits. Regular, monthly quality assurance checks will be conducted on the point-of-care devices, validated against central laboratory measurements.

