### Data analysis

As the initial focus of the intervention is on the management of depressive symptoms, we have considered the PHQ-9 as a main primary outcome, and will assess changes in PHQ-9 scores over 12-months between groups, adjusting for baseline PHQ-9 score, using a mixed effects multivariate model. For our second primary outcome of improvements in global disease control, we will employ a multivariate model that jointly tests the changes in multiple clinical outcomes, namely A1c, LDL cholesterol and systolic blood pressure [29]. Using the same analytic approach as in the recently published RCT of this intervention, we will apply a scaled marginal model [29,75] to simultaneously compare the change in these continuous outcomes at 12 months, adjusting for the baseline status for each variable. This approach scales the changes in each outcome by its standard errors, and thus the coefficients can be directly interpreted as effect sizes [29]. In either primary outcome analyses, the models will be estimated iteratively and the potential correlations among and between outcomes within individuals will be handled using generalized-estimating equation (GEE) models for each outcome [75].

We will also compare the study arms based on the proportion of subjects who achieved a remission of depression (i.e., PHQ-9 < 10 for 3 consecutive months) and the proportion of patients who achieve a clinically important change in the outcomes (that is, achieving a reduction of 5 points on the PHQ-9 [44] or a 10% or greater improvement over baseline values for A1C, LDL cholesterol and SBP at 12 months) [59,60], using generalized estimating equations and multivariable logistic regression models. This approach will allow us to present and interpret all outcomes in terms of absolute differences and a number-needed-to-treat [76].

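### Two responder rules are given for A1c, LDL cholesterol and SBP; the one analysed omits target achievement, so the target hypothesis has no analysis

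*Protocol article*

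**What the plan says.** The protocol article states the rule for the three cardio-metabolic markers twice.

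- Chronic disease-related clinical outcomes: the SBP, LDL cholesterol and A1c outcomes are "demonstrated by achievement of targets or significant improvements as indicated with a 10% improvement over baseline". Either limb is enough.
- Data analysis: the arms are compared on "the proportion of patients who achieve a clinically important change in the outcomes", spelled out for these markers as "a 10% or greater improvement over baseline values for A1C, LDL cholesterol and SBP at 12 months". There is no target limb. The two sections carry the same citations for the 10% criterion. The resulting proportions are to be presented as absolute differences and a number-needed-to-treat.

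Three other places bear on this.

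- Hypotheses: the intervention will "increase achievements of targets for cardio-metabolic measures".
- Patient management: Phase 2 of the intervention works "with a focus on reaching individualized targets for hemoglobin A1c, lipids and blood pressure measures". No numerical thresholds are given.
- Eligibility criteria: the only severity threshold for entry is "Score > =10 on the PHQ-9". None is set for A1c, LDL or SBP. The Background section describes the second efficacy trial as enrolling "individuals with depression and poorly controlled diabetes or heart disease", a restriction that is not carried over.

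**The concern.** The two sections can classify the same patient in opposite ways. The limb missing from the analysis is also the one that the hypothesis and the Phase 2 aim are about. As the Data analysis section stands, no comparison tests whether more patients reach target.

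Because patients may be controlled at entry, the 10% rule asks some of them for a further fall that their control may not call for. What is at stake is the meaning of the responder proportions and of the number-needed-to-treat. A non-responder may be a patient who failed to improve or a patient who was controlled throughout, and the reader cannot tell which.

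**Working it through.** The plan states no figure for this outcome, so there is nothing to reproduce. The check has two parts: where the rules disagree, and what follows from choosing one or the other. I read both rules marker by marker.

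**Where the rules disagree.** Let B be the baseline value, Y the 12-month value and T the target, with lower values better.

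- Outcome section: response if Y ≤ T or Y ≤ 0.9B.
- Data analysis section: response if Y ≤ 0.9B.

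They differ exactly when Y ≤ T and Y > 0.9B. That happens in two ways:

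1. B ≤ T: the patient is at target at entry and stays there without a further 10% fall.
2. B > T: the patient starts above target and reaches it with a change under 10%. This needs 0.9B < T, so B < T/0.9 = 1.11T, a baseline no more than about 11% above target.

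Missing data add a special case of the first kind. The Data analysis section carries the last observation forward, and the sample size section anticipates 40% attrition. A patient with only a baseline value has Y = B, which is always a non-response under the 10% rule. If that patient was at target at entry, the outcome section counts a success.

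**What follows from the choice.** The article does not give the share f at target at entry or any response rates for these markers, so what follows is illustration only. Assume f of 20% to 60%. Borrow 45% vs 60% as response rates among patients above target; the article gives those figures for depression remission. Assume first that every at-target patient stays at target without a further 10% fall.

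- 10% only: rate = (1 − f) × p
- Target or 10%: rate = f + (1 − f) × p

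| f | 10% only | Target or 10% | Difference, both rules | NNT |
|---|---|---|---|---|
| 20% | 36% vs 48% | 56% vs 68% | 12 points | 8.3 |
| 40% | 27% vs 36% | 67% vs 76% | 9 points | 11.1 |
| 60% | 18% vs 24% | 78% vs 84% | 6 points | 16.7 |

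The choice of rule moves each arm's rate by f, here 20 to 60 points. The difference is (1 − f) × 15 points under either rule, because f is added to both arms and cancels.

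Now let maintenance differ. Assume 80% vs 90% of at-target patients remain at target, and 10% of them in each arm improve by a further 10%. The 10%-only rate becomes (1 − f) × p + 0.10f. The composite rate becomes (1 − f) × p + f × m, with m = 0.80 or 0.90.

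| f | 10% only | Target or 10% |
|---|---|---|
| 20% | 38% vs 50%: 12 points | 52% vs 66%: 14 points |
| 40% | 31% vs 40%: 9 points | 59% vs 72%: 13 points |
| 60% | 24% vs 30%: 6 points | 66% vs 78%: 12 points |

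In this illustration the rules give different differences only when maintenance of target differs between arms. Patients of the second kind could also separate them, if one arm has more who reach target with a change under 10%.

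**The case against.** The strongest defence is that the Data analysis section describes a different endpoint on purpose. It is labelled as clinically important change and sits beside a 5-point PHQ-9 reduction. Both are measures of change, whereas target attainment is a measure of status. That reading is possible. But the two sections share their citations for the 10% criterion, and no other analysis takes up target attainment. On this reading the hypothesis still has no analysis.

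A second defence is that an article condenses the full plan, so numerical thresholds and stratified tables may properly sit in an analysis plan that is not shown. This stands for the threshold values, and their absence is not the point. It does not excuse two conflicting rules in the same article.

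A reader might also infer more than the text supports:

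- *That every patient at target at entry is counted as a failure.* Those who improve by a further 10% are still responders.
- *That omitting the target limb shrinks the difference and costs power by a known amount.* The dilution comes from keeping already controlled patients in the denominator. Under equal maintenance, restoring the limb leaves the difference where it was, as the first table shows. Every rate behind such a figure would be assumed.
- *That the primary disease-control result is affected, because it is built from the same markers.* The Data analysis section specifies continuous change in a scaled marginal model, adjusted for baseline. The primary PHQ-9 analysis is also of scores. Neither uses the responder rule.

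**Conclusion.** The point holds as an inconsistency in the definition of a secondary outcome. The article gives two responder rules for SBP, LDL and A1c, and the one it analyses leaves the target-achievement hypothesis untested. The rules disagree for patients who remain at target without a further 10% fall, and for those who reach target with a change under 10%. Nothing in the eligibility criteria keeps either group out.

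The effect on the result cannot be sized from the document. The tables show direction only and rest on an assumed share at target, borrowed response rates and assumed maintenance. They show that arm-level response rates can move a great deal with the rule, while the absolute difference and number-needed-to-treat need not move at all. The correction is worth making because it is cheap and gives a stated hypothesis an analysis, not because a loss of power has been demonstrated.

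**What to change.** 1. Reconcile the Chronic disease-related clinical outcomes and Data analysis sections to one definition.
2. For outcome classification only, apply the same prespecified threshold for each marker in both arms. The individualized Phase 2 goals are set with the care manager, whose active support usual-care patients do not have, so they cannot serve as a common yardstick. This concerns how results are counted, not how patients are treated.
3. Report by baseline status for each marker. Among patients above target at baseline, give the proportion reaching target or improving by 10%. Among those at target at baseline, give the proportion remaining at target.

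Adding target achievement to the whole-sample rule is not enough alone, since it turns automatic non-responders into automatic responders. In the at-target group, a baseline value carried forward counts as maintained by construction, so the table should show how many values were carried forward.

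The cost is one sentence and one extra table, with no new data. Each stratum is smaller: with 60 per arm and 20%, 40% or 60% at target at entry, 48, 36 or 24 patients per arm remain in the above-target group (60 × 0.8, 0.6 or 0.4).

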For all analyses we will employ an intention-to-treat framework for our primary analysis, using a last-observation-carried-forward method of imputation for subjects who do not have complete follow-up data for primary or secondary outcomes. This approach is conservative as it assumes subjects with missing follow-up data have not changed. In either case, the regression models will accommodate additional covariates, as required, to adjust for PCN site, as well as any post-allocation baseline differences between groups in clinically important (e.g., age, sex) or statistically significant (e.g., p < 0.1) characteristics. This ability to statistically control for potential imbalance may be necessary given the non-random treatment allocation used in our “on-off” design.

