### Sample size and power considerations

We estimate that a minimum total sample size of 120, with 60 in each arm, would provide power of 0.80 to detect a mean difference of 5 points in the PHQ-9 [44], assuming a repeated measures correlation of 0.6, and 2-tailed alpha of 0.05. This sample size also provides more than 80% power (two sided alpha = 0.05) to detect any between-group absolute difference in proportions of 15% or more (e.g., 45% of usual care patients achieve depression remission vs 60% of intervention patients) [29]. Anticipating a 40% attrition rate, we planned to recruit 168 patients in total across our 4 PCN sites. Although the model is implemented in 4 PCN sites, the individual general physicians affiliated with the PCN will carry out the changes in care. While we will include PCN site as a covariate in our analysis, because there are approximately 140 general physicians across these 4 PCN sites, we choose not to further inflate our sample to account for clustering of patients and their outcomes.

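### The plan makes last observation carried forward the primary imputation and calls it conservative, but that holds only if dropout is similar in both arms and treatment effects are stable

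*Protocol article*

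**What the plan says.** The Data analysis section of the protocol article places the primary analysis in an intention-to-treat framework, "using a last-observation-carried-forward method of imputation for subjects who do not have complete follow-up data for primary or secondary outcomes". The reason given is: "This approach is conservative as it assumes subjects with missing follow-up data have not changed".

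The same section says that PHQ-9 change over 12 months will be compared with adjustment for baseline, "using a mixed effects multivariate model". It then says that in both primary analyses the within-person correlations will be handled by generalized estimating equations (GEE).

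Other sections bear on the point:

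- Outcome measures: all outcomes are taken at baseline, 6 and 12 months.
- Eligibility criteria: entry requires a PHQ-9 score of 10 or more.
- Sample size and power considerations: "Anticipating a 40% attrition rate, we planned to recruit 168 patients in total across our 4 PCN sites". The worked example there has 45% of usual-care patients and 60% of intervention patients reaching remission.

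No dropout rate by arm is given.

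**The concern.** Two parts of the justification fail against the protocol's own design.

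First, the sentence describes baseline carried forward. With a 6-month visit, anyone lost between months 6 and 12 contributes the 6-month score as if it were the 12-month result. An early gain is then credited at 12 months whether or not it lasted.

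Second, assuming no change is conservative for a between-arm contrast only if it penalises the intervention at least as much as the control. Patients are selected on a high score, and the planning example expects 45% of usual-care patients to remit, so improvement is expected in both arms. Holding dropouts at an earlier, worse score therefore penalises whichever arm loses more patients.

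Unequal loss is plausible. Intervention patients have care-manager contact once or twice a month, and usual-care patients have no such added support. At stake are the size, and in unfavourable cases the direction, of the error in the PHQ-9 comparison.

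**Working it through.** **The plan's own figures.** 120 × 1.4 = 168 reproduces the recruitment target. Forty percent loss from 168 leaves 168 × 0.6 ≈ 101; retaining 120 of 168 corresponds to (168 − 120)/168 = 28.6% loss. The protocol is thus consistent with anything from about 29% to 40% missing, and 40% is the figure it states.

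**Inputs from the protocol.** 168 patients, taken as 84 per arm (equal split assumed); correlation 0.6; two-sided alpha 0.05; visits at 0, 6 and 12 months; 40% attrition.

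**Inputs assumed.** PHQ-9 SD 5 (not stated; 60 per arm, 5 points and 80% power back-solve to 9.8, used as the upper value). Usual-care improvement m6 = 3 points by month 6 and m12 = 4 by month 12. Dropout depends on arm only. A share q = 0.4 of dropouts leaves after month 6, so 60% leave before it.

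**Expected LOCF result with no treatment effect.** An arm with dropout d shows mean improvement (1 − d)·m12 + d·q·m6. With dropout dU in usual care and dI in the intervention arm, the spurious benefit is

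(dU − dI) × (m12 − q·m6).

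With the values above, m12 − q·m6 = 4 − 0.4 × 3 = 2.8. Type I errors are from simulated baseline-adjusted ANCOVA on the LOCF-completed month-12 score:

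| Dropout, intervention/usual care | Spurious benefit (points) | Type I error |
|---|---|---|
| 40%/40% | 0 × 2.8 = 0 | about 5% |
| 35%/45% | 0.10 × 2.8 = 0.28 | 7% |
| 30%/50% | 0.20 × 2.8 = 0.56 | 16% (8% at SD 9.8) |
| 30%/50%, all before month 6 (q = 0) | 0.20 × 4 = 0.80 | 29% |

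The bias depends on the difference in dropout, not on its overall level. It also scales with the assumed improvement. With all dropout early and a 30%/50% split, a usual-care improvement of 3 to 7 points gives 0.20 × 3 = 0.6 to 0.20 × 7 = 1.4 points, with type I error of 20% to 47%.

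**True benefit of 2.5 points, equal 40% dropout.** The LOCF estimate is 0.6 × 2.5 + 0.4 × 0.4 × e6, where e6 is the month-6 benefit. If e6 follows the same time course (2.5 × 3/4 = 1.875), this is 1.50 + 0.30 = 1.8; if e6 is already 2.5, it is 1.9. At 28.6% loss the first figure is 0.714 × 2.5 + 0.286 × 0.4 × 1.875 = 2.0.

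**True benefit of 2.5 points, more loss in the intervention arm (50%/30%).** With e6 = 1.875 the intervention arm shows 0.5 × 6.5 + 0.5 × 0.4 × 4.875 = 4.23, and usual care shows 0.7 × 4 + 0.3 × 0.4 × 3 = 3.16. The estimate is 1.07, so more than half of the benefit is lost.

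**Remission, using the protocol's 45% and 60%.** A carried entry score is at least 10 and cannot count as remission. If all dropouts are so classified:

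- Equal 40% loss: 45% × 0.6 = 27% versus 60% × 0.6 = 36%, a difference of 9 points instead of 15.
- 45% in both arms, loss 50% usual care and 30% intervention: 22.5% versus 31.5%, a false 9 points.
- 45% versus 60%, loss 30% usual care and 50% intervention: 31.5% versus 30%, so the effect vanishes.

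**Comparison.** In the ANCOVA scenarios above, the same model on observed month-12 data gave about 0 points under the null with type I error near 5%, and about 2.5 points when that was the truth.

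**The case against.** The strongest reply is that the protocol gives one attrition rate and no split by arm. With equal dropout and a stable effect, LOCF keeps type I error near 5% and shrinks a real effect, which is what the authors claim. A moderate 35%/45% split gives only 7%, and a larger SD lowers the inflation further. This stands. It limits the size of the problem but does not rescue an unconditional claim of conservatism.

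The observed-data comparator is also favoured by construction, because simulated dropout depended on arm alone. In a check where dropout in usual care depended on the unseen 12-month score, under no effect, observed-data ANCOVA was off by 1.11 points (type I error 28%) and LOCF by 0.35 (9%). So LOCF is not worse in every setting. The recommended mixed model was not itself simulated.

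Three stronger readings are tempting, and the document does not support them:

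- That both primary outcomes are shown to be biased. The argument from selection rests on PHQ-9; there is no entry threshold for A1c, LDL cholesterol or systolic pressure, and nothing was computed for the combined outcome.
- That imputation is redundant because a mixed model is already planned. The Data analysis section also invokes GEE for both primary outcomes, and unweighted GEE lacks the missing-at-random property of a likelihood fit.
- That the standard errors are materially wrong. Imputed values are treated as observed, but type I error near 5% under equal dropout shows no material distortion there; the inflation reported comes from bias.

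**Conclusion.** The point holds in a conditional form. The stated justification is incorrect: LOCF does not assume no change for patients with a 6-month visit, and it is not generally conservative when usual care is expected to improve. It only attenuates when dropout is similar across arms and effects are stable. Otherwise the direction of bias in PHQ-9 follows the arm that loses more patients.

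A reader might infer that LOCF will produce a false positive in this trial. The protocol does not support that, since attrition by arm is unknown. The figures illustrate what can happen: type I error from about 5% (equal dropout) through 7% and 16% to 29% in the most adverse main scenario, and a true 2.5 points reduced to about 1.8 with equal dropout. They rest on the assumed SD, usual-care improvement, dropout split and timing, and on dropout unrelated to outcome within arm. Confidence is high that the claim is wrong and lower on the magnitude.

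**What to change.** 1. **PHQ-9.** State that the mixed model is fitted by likelihood to all observed baseline, 6- and 12-month scores, with the month-12 between-arm contrast as the primary estimate and no single imputation. Reword the GEE sentence so that it no longer applies to this outcome.
2. **Scaled marginal model and responder analyses.** Where GEE or logistic models are used, apply multiple imputation that includes the 6-month values.
3. **LOCF.** Keep it at most as a sensitivity analysis.
4. **Wording.** Delete the statement that the approach is conservative.

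A delta-adjusted analysis for data missing not at random would be a useful optional addition; its absence from an article is not a fault.

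The cost is some extra programming and plan wording, with no added patients, visits or data. The downside is reliance on a missing-at-random assumption, which outcome-related dropout could violate.

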### Recruitment and allocation

Recruiting participants into TeamCare-PCN involves three steps. * First *, a screening survey accompanied with an endorsement letter from the PCNs will be mailed out to all patients with type 2 diabetes on the PCNs’ diabetes registries. This survey asks about age, the ability to read and speak English, having type 2 diabetes, length of time since diagnosis, and screens for depressive symptoms. * Second *, after potential participants have completed and returned the screening survey, PCN staff will contact eligible participants to confirm all eligibility criteria and if the participant is willing to participate, and schedule a baseline assessment visit. * Third *, during the baseline visit, the Care Manager (CM) will confirm eligibility, explain the intervention, provide an intervention-specific information letter and obtain a signed written informed consent from the patient to participate in the study.

Participants will be allocated to study groups using a previously successful “on-off” group assignment method (Figure 1) [39,41,42]. Eligible and consenting respondents who book for a baseline assessment with the CM during month 1 will be allocated to the intervention arm (ON-group). Those who book the baseline assessment in month 2 will be allocated to the usual care arm (OFF-group). This allocation process will continue until the target sample size is recruited. This method has been used in many quality improvement studies, reliably leads to balance in measured [and unmeasured] patient characteristics [39,41,42], and meets study design criteria for internal validity sufficient to permit inclusion in the Cochrane Collaborations’ Effective Practice and Organization of Care (EPOC) systematic reviews [40]. Because all four sites are involved in both “on” and “off” phases, this particular study design also balances case mix and controls for Hawthorne or volunteer effects, as well as issues related to “institutional learning” over time [39,40,42].

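### Part of the adjustment set is chosen after allocation by baseline significance tests (e.g. p < 0.1), in a non-random design that relies on that adjustment

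*Protocol article*

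**What the plan says.** Under Recruitment and allocation, the arm follows from the calendar month in which the baseline visit is booked: month 1 is intervention, month 2 is usual care, and so on in alternation until the target is reached.

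The Data analysis section fixes some covariates outright. The PHQ-9 model is described as "adjusting for baseline PHQ-9 score, using a mixed effects multivariate model", and the model for A1c, LDL cholesterol and systolic blood pressure as "adjusting for the baseline status for each variable". The section on sample size adds that "we will include PCN site as a covariate in our analysis".

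The rest is conditional. Data analysis says that "the regression models will accommodate additional covariates, as required, to adjust for PCN site", and then extends this to "any post-allocation baseline differences between groups in clinically important (e.g., age, sex) or statistically significant (e.g., p < 0.1) characteristics". The reason follows: "This ability to statistically control for potential imbalance may be necessary given the non-random treatment allocation used in our" on-off design.

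So there are three routes into the model: fixed (baseline outcome values, site), clinical importance of an observed difference (age and sex as examples), and statistical significance of an observed difference (p < 0.1 as an example).

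**The concern.** The third route selects covariates by the wrong property. Confounding depends on how far a variable differs between arms and how strongly it predicts the outcome. A baseline p-value reflects only the first, and mixes it with sample size. At this trial's size, a prognostic variable with a real but modest imbalance can easily fail the test and stay out, while a variable that predicts nothing can pass by chance and go in.

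In a randomised trial this would be mainly inefficient. Here a month-by-month allocation can produce systematic differences, and the protocol itself presents covariate adjustment as its remedy. The second route could cover the gap, but its list consists of examples, and it too is triggered by a difference seen after allocation. The final covariate set is therefore not known until the arms have been compared. At stake are some residual bias, some lost precision, and a primary model that cannot be written down in advance.

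**Working it through.** **Inputs from the protocol article.** Planned recruitment is 168, which is the stated minimum of 120 inflated by 40%: 120 × 1.4 = 168. With equal arms this is 84 per arm at baseline. The stated minimum is 60 per arm. The screening level is p < 0.1, two-sided. The article gives no operating characteristics for this screen, so there is no figure of its own to reproduce.

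**Assumptions, not in the article.** True standardised imbalance of 0.20 to 0.50 SD; covariate-outcome correlation r of 0.3 to 0.5; PHQ-9 SD of 5 points, used only to convert to points.

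**1. Sensitivity of the screen.** For a true imbalance d with n per arm, P(p < 0.1) = Φ(d√(n/2) − 1.645) + Φ(−d√(n/2) − 1.645). For d = 0.20 and n = 84: 0.20 × √42 = 1.296, giving about 0.36.

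| True imbalance (SD) | Flagged, 84 per arm | Flagged, 60 per arm |
|---|---|---|
| 0.20 | 36% | 29% |
| 0.25 | 49% | 39% |
| 0.30 | 62% | 50% |
| 0.40 | 83% | 71% |
| 0.50 | 94% | 86% |

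To be flagged, an observed difference must exceed 1.645 × √(2/n), which is 0.254 SD at 84 per arm and 0.300 SD at 60 per arm. For a binary characteristic at 84 per arm, 50% against 60% is flagged 37% of the time.

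**2. Bias from one measured confounder.** Without adjustment the bias is d × r: from 0.20 × 0.3 = 0.06 SD to 0.30 × 0.5 = 0.15 SD. Simulation with 84 per arm, no treatment effect and 20,000 runs per setting gave these mean biases:

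| d, r | No adjustment | p < 0.1 rule | Always adjusted |
|---|---|---|---|
| 0.20, 0.3 | 0.058 | 0.019 | about 0 |
| 0.20, 0.5 | 0.100 | 0.036 | about 0 |
| 0.25, 0.5 | 0.125 | 0.035 | about 0 |
| 0.30, 0.5 | 0.150 | 0.027 | about 0 |

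Under the rule the residual is thus about 0.02 to 0.04 SD. At an SD of 5, 0.04 × 5 = 0.2 PHQ-9 points. The two-sided rejection rate stayed near 5% (5.2% at d = 0.25, r = 0.5, both under the rule and with constant adjustment).

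**3. Several confounders.** With independent covariates, each imbalanced by 0.2 SD with r = 0.3 and 84 per arm, three of them gave a bias of 0.064 SD and a rejection rate of 6.4% under the rule. Five gave 0.107 SD and 9.4%, against 0.001 SD and 5.1% with all five fixed.

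**4. Precision.** With three balanced covariates (r = 0.3), the rule gave an empirical standard error of 0.147, against 0.135 when they were always included.

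**5. Chance inclusions.** Among 10 independent, balanced characteristics, at least one is flagged with probability 1 − 0.9^10 = 65%; among 20, 1 − 0.9^20 = 88%.

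**6. Enrolment time (secondary).** With even accrual over 12 months, ON months 1, 3, …, 11 have mean 6 and OFF months 2, 4, …, 12 have mean 7: a one-month difference. Relative to the spread of enrolment dates this is 0.29 SD over 12 months and 0.14 SD over 24. An annual cycle balances over whole years. The article gives no recruitment length.

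**The case against.** The strongest reply is that the p-value is only one of three routes. The baseline outcome, usually the strongest predictor, is always in the model, and so is site. A difference in age or sex can enter whatever its p-value. This stands. It confines the sensitivity and bias figures to other prognostic covariates, and r must be read as correlation remaining after the fixed covariates, which makes the upper end of 0.3 to 0.5 less likely. It does not remove the point, because the clinical list is left open and nothing says which variables it contains.

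A second reply is that the harm is small. For one confounder that is right: the larger imbalances are the ones the screen catches, and the type I error hardly moves. The residual matters only if several modest imbalances point the same way.

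Third, a reader might infer that the model is chosen by people who know the allocation. The Data management section says that investigators, research assistants and analysts stay masked, so the document does not support that. Masking limits discretion, but it does not fix the covariate set.

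Fourth, a reader might treat the absence of a calendar-time term or of month clustering as a major flaw. Monthly alternation at all four sites already balances long trends and season closely, and such modelling detail may sit in a fuller plan. Clustering by site and month would matter little: 168 patients over an assumed 12 to 24 months is 7 to 14 a month, or 1.75 to 3.5 per site-month. With an assumed intraclass correlation of 0.01 to 0.02, variance rises by 0.75 × 0.01, about 1%, to 2.5 × 0.02 = 5%. The statement "we choose not to further inflate our sample to account for clustering of patients and their outcomes" concerns physicians, not allocation months.

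**Conclusion.** The point holds in a limited form. The protocol states a rule under which part of the adjustment set depends on baseline significance tests made after allocation, in a design where it says adjustment may be needed. For covariates outside the fixed set, and outside whatever is judged clinically important, the screen is insensitive to small-to-moderate imbalance: 36% to 62% detection for 0.20 to 0.30 SD at 84 per arm. The cost is about 0.02 to 0.04 SD of bias per measured confounder, more if several act together, plus some lost precision. The bias and precision figures rest on the assumed imbalances and correlations; the detection rates rest only on sample size, threshold and imbalance.

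Two stronger readings should be resisted. One is that the screen misses most moderate confounding: at 84 per arm it misses more than half only up to about 0.25 SD (about 0.30 SD at 60 per arm), and at 0.40 to 0.50 SD it flags 83% to 94%. The other is that site is the only adjustment, which the fixed baseline outcome values contradict. This is a worthwhile correction to the analysis wording, not a threat to the trial's main conclusion on its own.

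**What to change.** Delete the p < 0.1 trigger and the open wording around it. Name the adjustment set in advance on prognostic grounds, from baseline data already collected:

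- baseline value of the outcome and PCN site (already fixed);
- age and sex, made unconditional;
- time since diabetes diagnosis, which the screening survey asks for;
- baseline antidepressant use, if it is recorded in both arms. The article lists medication use as a process indicator but does not show that it is captured at baseline for usual-care patients.

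Report baseline characteristics by arm with standardised differences and no tests. Any further covariates belong in a labelled sensitivity analysis.

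Optionally, add a smooth term for enrolment date, since ON months always come first. Terms for on/off month pairs would leave the one-month offset in place, and month as a categorical factor cannot be fitted because month determines the arm.

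The cost is a change of wording and a few degrees of freedom. If baseline antidepressant use is missing in one arm, it is simply left out of the set.
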